### Interventions

**
Intervention arm: Yoga-based intervention for maternal Mental health and iMmunity (Yoga-M
_2_)
**

Participants randomized to the intervention arm will attend weekly supervised group yoga sessions and will also be requested to practice yoga regularly at home for a total duration of three-months. Group yoga session will be for 60 to 75 minutes. A typical session will begin with an introduction of the participants, a brief overview of the session by the yoga instructor and an opening prayer. This will be followed by
*sukshma-vyayam* (micro-circulation exercises) for 10 minutes,
*asanas* in standing, sitting, and supine position for 15 minutes,
*pranayama* for 15 minutes followed by
*shavasana* (deep relaxation) for 10 minutes. The session will end with a closing prayer. A detailed description of the yoga session is provided in
Table 1. After the session ends, the yoga instructor will spend time with each participant individually and suggest changes/modifications based on any problems they might have in practicing any of the yoga-based activities. Weekly group sessions will be conducted either in-person or online. In-person sessions will be preferred if allowed, depending on the COVID-19 pandemic-situation in the study area and restrictions in place. In-person sessions will be in a well aerated and ventilated hall. Use of sanitizers where appropriate and physical distancing will be maintained during yoga sessions. Participants can also attend group yoga sessions online via
Zoom. The plan is to have five in-person group yoga sessions over five days in the beginning to teach the entire yoga sequence to the participants. This will be followed by weekly group yoga sessions. We anticipate that each participant will attend 10 group yoga sessions over 12 weeks.

**Table 1. T1:** Yoga-based intervention for maternal Mental health and iMmunity (Yoga-M
_2_).

	Type of Activity	Duration (Second Trimester)	Duration (Third Trimester)
**1.**	**Opening Prayer** ‘Om, Sahana Vavatu Sahana Bhunattu Saha Viryam Karawavahai Tejasvinavaditamastu Ma vidvishavahai Om, Sāntih Sāntih Sāntih’	**3 minutes**	**3 minutes**
2.	** *Sukshma-Vyayam* ** **(Micro-circulation exercises)**	**10 minutes**	**5 minutes**
	*Griva Sanchalan* Neck movements	Yes	Yes
	*Skandha Paribhraman* Shoulder rotation	Yes	Yes
	*Hasta Ayama Svasanam* (Hands in and out breathing)	Yes	Yes
	*Hasta Vistara Svasanam* (Hands stretch breathing)	Yes	Yes
	*Gulpha Vistara Svasanam* (Ankle stretch breathing)	Yes	Yes
	*Karna Sanchalan* Ear movements	Yes	Yes
	*Skandha Svasanam* Shoulder movements	Yes	Yes
	*Parshva Skandha Svasanam* Shoulder cross movements	Yes	Yes
	*Hastottan Svasanam* Arms over head movements	Yes	Yes
	*Vyaghra Svasanam* (Tiger breathing)	Yes	No
	*Setu Bandha Svasanam* (Bridge posture breathing)	Yes	No
**3.**	** *Asana* (Postures)**	**15 minutes**	**10 minutes**
	**Standing *Asanas* **		
	*Tadasana* (Tree pose)	Yes	Yes
	*Ardhakati Chakrasan* (Lateral arc pose)	Yes	Yes
	*Trikonasan* (Triangle pose)	Yes	Yes
	**Sitting *Asanas* **		
	*Vajrasana* (Ankle pose)	Yes	Yes
	*Vakrasana* (Spine twist pose)	Yes	No
	*Siddhasana* (Sage pose)	No	Yes
	*Baddhakonasana* (Bound ankle pose)	No	Yes
	*Upavistakonasana* (Spread legs pose)	No	Yes
	*Malasana* (Garland pose)	No	Yes
	**Supine *Asanas* **		
	*Viparita Karani* (Half shoulder stand)	Yes	No
	*Supta-baddha Konasana* (Folded leg lumbar stretch)	Yes	Yes
**4.**	** *Pranayama and* Meditation**	**10 minutes**	**20 minutes**
	*Vibhagiya Pranayam* Sectional breathing	Yes	Yes
	*Anulom-Vilom Pranayam* (Alternate nostril breathing)	Yes	Yes
	*Sheetali Pranayam* (Cooling breath)	Yes	Yes
	*Bharamari* (Humming breath)	Yes	Yes
	*Nadanusandhana* (Mind-sound resonance)	Yes	Yes
**5.**	** *Dirgha Vishranti Paddhati* ** **Deep Relaxation Technique**	**10 minutes**	**15 minutes**
**6.**	**Closing Prayer** ‘Om, Sarve Bhavantu Sukhinah, Sarve Santu Nirāmayāh Sarve Bhadrāni Paśyantu, Mā kascit Duhkha Bhāgabhavet Om, Sāntih Sāntih Sāntih’	** 2 minutes**	** 2 minutes**
	**Total Duration**	**50 minutes**	**55 minutes**

In addition to the weekly supervised group sessions, participants will be encouraged to practice the yoga sequence at home daily for at least 30 minutes. The yoga instructor will work with each participant and help them develop their home practice schedule. A booklet containing a detailed description of each of the included activities and a photograph of that activity will be provided to participants. The contents of the booklet and the videos explaining the Yoga-M
_2_ sequence will also be uploaded on the project website and participants will be explained to about how to access this material. A token amount will be paid to each participant in the Yoga-M
_2_ arm (INR 100 per session) to cover travel expenses for attending in-person yoga sessions. Group yoga sessions will be facilitated by certified and experienced women yoga instructors. During the sessions, they will provide particular emphasis on, a) awareness of breath, b) focus on bodily sensations during each of the yoga activities, and c) avoiding injuries due to yoga practice.

In addition to the yoga practice, participants will be provided educational leaflets containing information about physical activity, sleep, and diet during pregnancy.

Yoga-M
_2_ is based on the Integrated Approach for Yoga Therapy during pregnancy (IAYT-P)
^
19
^. This intervention was earlier evaluated using a randomized controlled trial design in an urban population in Southern India. The participants were recruited from a hospital in Bengaluru city. Women in the 20
^th^ week of normal pregnancy were randomly assigned to receive IAYT-P group (n=51) or standard antenatal exercises (n=45). In the yoga group, there was reduction in Pregnancy related Experience (PEQ) by 26.9%, reduction in state anxiety by 15.6% and a decrease in depression by 30.7%. In the control group, there was an increase in state anxiety by 13.8% and an increase in depression by 3.6%
^
19
^.

Adaptations to IAYT-P were essential to include activities to improve immune function and tailor the delivery of the intervention for a rural context affected by COVID-19 crisis. This was done by reviewing the literature, undertaking a qualitative study with pregnant women and community health workers, and conducting an intervention adaptation workshop with pregnant women.
Table 2 provides the summary of the intervention adaption process.

**Table 2. T2:** Intervention adaptation process. IAYT-P: Integrated Approach for Yoga Therapy during pregnancy. MDNIY: Morarji Desai National Institute for Yoga. PIMS: Pravara Institute of Medical Sciences.

Method	Description	Changes made to IAYT-P
**Literature** ** review**	• Interventions used in previous studies (included in systematic review by Falkenberg *et.al*., ^ 11 ^) assessing the effect of yoga on immune function were reviewed in detail. • A book titled, ‘Yoga as Medicine: The Yogic Prescription for Health and Healing,’ by [name] ^ 20 ^ was referred. • Yoga manual for pregnant women developed by the MDNIY ^ 21 ^ was referred.	• Neck movements included in the manual by MDNIY were added. • Shoulder movements were added as they likely improve the flow of lymph ^ 20 ^. • Advice on diet, sleep hygiene and physical activity was added.
**Qualitative ** **Study**	• 10 in-depth interviews with pregnant women to explore facilitators and barriers to yoga practice • Three focus group discussions with community health workers to assess the feasibility of conducting group sessions in the community settings.	• Community hall or *anganwadi* center to deliver group yoga sessions instead of a hospital setup as pregnant women preferred a location close to their homes. • Modifications in a few *asanas* as some pregnant women will be able to attend the sessions wearing *saree* (a long piece of cloth draped around the body and over one shoulder, worn by women in India). • Recruitment of participants in the antenatal clinical of PIMS, as the community health workers suggested that treating obstetrician should approve the practice of yoga by pregnant women.
**Intervention ** **Adaptation ** **Workshop**	• Two intervention adaptation workshops; one with four pregnant women and other with three pregnant women were conducted to get their feedback on the modified yoga sequence.	• No changes were made in the modified sequence as all the participants provided positive feedback on the modified yoga sequence.

**
Comparison arm: Enhanced Usual Care (EUC)
**

Participants randomized to the EUC arm will receive a single session of health education delivered by the Intervention Coordinator (IC). During this session, aspects related to sleep hygiene and diet during pregnancy will be discussed and they will be encouraged to undertake regular physical activity (150 min/week). They will be provided educational leaflets containing information about physical activity, sleep, and diet during pregnancy. The IC will work with the participants to identify ways to reduce stress during pregnancy and improve social support. As per the current standard of care in the antenatal clinic of Department of Obstetrics, pregnant women are neither screened for stress nor is there any discussion about improving mental health during pregnancy. Participants with moderate stress (Perceived Stress Scale score > 13) will be referred to a psychiatrist in PIMS.

**
Criteria for discontinuing or modifying allocated interventions
**

If there is spontaneous abortion or stillbirth, participation in both the arms will be discontinued. Other than this, there is no specific criteria to discontinue Yoga-M
_2_ intervention. A few modifications in the sequence for individual participants may be done by the yoga instructor based on feedback from them. Obstetrician may advise participants to discontinue yoga due to health issues or they may decide to stop practicing yoga themselves for any reason.

**
Strategies to improve adherence to interventions
**

The IC and the yoga instructor will regularly contact participants in Yoga-M
_2_ arm to coordinate attendance in weekly group yoga sessions. If a participant misses two consecutive weekly group yoga sessions, the IC will visit the participant at home to address any barriers related to joining the session. Adherence to home practice will be assessed using home practice logs. 

**
Relevant concomitant care permitted or prohibited during the trial
**

Throughout the duration of the trial, participants will receive usual care and no specific component of antenatal care or other health services will be prohibited.

**
Provisions for post-trial care
**

Participants in both arms will receive information about yoga classes they can join after the end of the trial. Participants in the control arm will also receive the yoga intervention booklet and the audio-visual material. Participation in yoga classes post-trial will be entirely voluntary and on a self-pay basis. No compensation will be provided to participants who suffer non-negligent harm from trial participation.

**
Outcomes
**

Outcome assessment will include measures related to:

a) feasibility and acceptability of yoga-based intervention (Yoga-M
_2_) deliveryb) preliminary efficacy of Yoga-M
_2_

Feasibility and acceptability will be assessed using the following process data:

1. Number and proportion of eligible participants who are recruited per week in each arm.2. Number and proportion of recruited participants in Yoga-M
_2_ arm who attend the in-person yoga sessions.3. Number and proportion of recruited participants in Yoga-M
_2_ arm who attend at least 50% of the follow-up yoga sessions.4. Number and proportion of recruited participants who complete follow-up assessment three-months post-randomization in each arm.

Process data will be collected from the study enrollment logs and intervention delivery logs. Study enrollment logs will be maintained by RAs and intervention delivery logs will be maintained by the IC. Every week this data will be manually entered and stored as CSV files on an access-restricted computer.

Assessment of acceptability of the intervention will also be done using a structured satisfaction survey and a qualitative study. In-Depth Interviews (IDIs) with all yoga instructors and enrolled participants will be completed. Semi-structured interviews will cover themes related to the delivery, content, comfort, and complexity of the intervention. We plan to enroll around 15 participants (10 from the intervention arm and 5 from the control arm), however, the sample size for the qualitative study will be determined by data saturation.

The description of measures which will be used to assess the preliminary efficacy of the intervention is given in
Table 3.

**Table 3. T3:** Measures to assess the preliminary efficacy.

Outcome	Measure	Time-point
Stress	Perceived Stress Scale (PSS)	Baseline and three-months post-randomization
Quality of Life	EuroQoL 5 Dimensions Score (EQ-5D-5L)	Baseline and three-months post-randomization
Immune Function	Wisconsin Upper Respiratory Symptom Severity Scale	Baseline and three-months post-randomization
Immune Function	Serum C-Reactive Protein	Baseline and three-months post-randomization
Injuries due to yoga	Self-report log	Every week for three-months post-randomization
Serious Adverse Events (SAE)	SAE report form	Baseline and three-months post-randomization

**
Perceived Stress Scale (PSS)
**

Perceived stress will be measured using 10-item version of the original scale
^
22
^. The items in this instrument assess how unpredictable, uncontrollable, and overloaded participants appraise the situations in their lives in last one month. PSS has been widely used in research studies across the globe and it has acceptable psychometric properties
^
23
^. In this study, we will use the Marathi version of the PSS which was translated from the English version using the World Health Organization (WHO) guidelines for the process of translation and adaption of instruments
^
24
^.

**
EuroQoL 5 Dimensions Score (EQ-5D-5L)
**

European Quality of Life Five Dimension (EQ-5D-5L) descriptive system will be used to measure Health related Quality of Life (HRQoL). A single utility score will be calculated using the value set/preference weights for Thailand as the Eq-5D value set for India is under development
^
25
^. Participants will also provide an overall evaluation of their health using a visual analogue scale (VAS). We will use the Marathi version of EQ-5D-5L with permission from the EuroQoL Group
^
26
^. The EQ-5D has been validated in different parts of the world
^
27
^. 

**
Wisconsin Upper Respiratory Symptom Severity Scale (WURSS)
**

The incidence and severity of upper respiratory tract infections in the participants will be assessed using the
Wisconsin Upper Respiratory Symptom Survey (WURSS-21). This is a 21-item scale; 10 items assess symptoms, nine items assess functional impairments, and there is one item each to assess the overall severity and change. Responsiveness, reliability, convergence, and importance to patients of this scale have been validated
^
28
^. Participants will complete WURSS-21 at the end of each day in the study. We will use the Marathi version of WURSS with permission from the developers.

**
Serum C-Reactive Protein (CRP)
**

Serum CRP levels will be determined using fixed-point immune-rate method (VITROS 250/350/5, 1 FS/4600/XT 3400 Chemistry Systems and the VITROS 5600/XT 7600 Integrated Systems). The limit of detection for VITROS Chemistry Products CRP slides is 2.72 mg/L.

**
Self-report log
**

Participants in both arms will maintain a log to document any injuries/non-serious adverse events during the duration of the trial.

### Participant timeline

Participant’s timeline through the trial is presented in
Figure 1.

**Figure 1. f1:**
[figure not shown]
Participant flow diagram through the pilot randomized trial.

### Sample size

We anticipate that the standardized effect size between the two arms will be small (0.2). Hence, we plan to recruit 25 pregnant women in each arm (total=50) based on the recommendations by Whitehead
*et al.*
^
29
^.

### Recruitment

Participants will complete baseline assessment using a questionnaire after providing the informed consent. RAs will administer this questionnaire and it will include data on demographic and socio-economic measures and the primary and secondary outcome measures. The IC will then undertake treatment allocation in a separate room. The IC will work independently of RAs who will not be aware about the treatment allocation.

### Assignment of interventions: allocation

**
Sequence generation
**

An independent statistician will generate randomization list using the statistical program
R (version 3.6.1). First, a list of variable block sizes (randomly selected block sizes of 2/4/6/8) will be created followed by a list of intervention allocation (Yoga-M
_2_ or EUC) using a 1:1 allocation ratio. The list will be shared with the Clinical Research Coordinator (CRC) based in the Directorate of Research, PIMS. They will prepare serially numbered, opaque, sealed envelopes using the randomization list.

**
Concealment mechanism
**

Participants will be randomly allocated to the intervention group by the IC using serially numbered, opaque sealed envelopes after they complete their baseline assessment.

**
Implementation
**

The IC will collect a set of opaque sealed envelopes from CRC as per the serial numbers, a few hours prior to the recruitment. The IC will open the opaque sealed envelopes (as per the serial numbers) in front of the participants and immediately inform them about the intervention group (i.e., Yoga-M
_2_ or EUC) they have been assigned to. Participants will be requested to not reveal their group assignment to the RAs at the three-month follow-up assessment. To maintain allocation concealment, neither the RAs nor any staff working at the hospital will have access to the randomization lists. The IC will inform the CRC the unique identification number of the participant (and no other details) and the intervention allocation group. The CRC will maintain the record of intervention allocation.

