### Assignment of interventions: blinding

**
Who will be blinded?
**

Participants, their family members, and study team members involved with intervention delivery (IC and yoga instructors) will be aware of participants’ assigned intervention during the trial. It is not possible to avoid bias arising due to this. RAs will complete baseline and three-month follow-up assessments, and they will not interact in any way with the intervention team. RAs will not be aware of the intervention allocation status. Participants and family members will be instructed not to disclose whether they are receiving the intervention to the RAs at the time of three-month follow-up assessment. Additionally, RAs will also remind participants not to reveal their group assignment to them so that they remain blind to the treatment allocation of participants.

Obstetricians will not be aware of the intervention allocation status, minimizing the risk of any change in their behavior while dealing with the participants.

The intervention team led by the IC and the outcome assessment team comprising of RAs will not have any interactions during the trial. They will work independently of each other in separate locations and will have no communication about trial participants and their intervention allocation status. During the training of RAs in the outcome assessment team, special emphasis will be given to explaining the equipoise between the two interventions.

We will monitor the risk of contamination at the level of the yoga instructors, intervention coordinator, and participants. Yoga instructors and the intervention coordinator will be requested to not share the information about Yoga-M
_2_ with pregnant women other than those enrolled in the intervention arm (Yoga-M
_2_). They will also ensure that participants in both the arms adhere to the group randomly allocated to them.

**
Procedure for unblinding if needed
**

In case there is any yoga-related adverse event, allocation of intervention group will be revealed to obstetrician.

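### The unblinded Intervention Coordinator holds, opens and reports the envelopes, and no stated step ties a woman's ID to an envelope serial number before opening

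*Protocol article*

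**What the plan says.** The protocol article sets out the allocation chain in Recruitment and in Assignment of interventions: allocation.

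- **List and envelopes.** An independent statistician makes the list in permuted blocks ("randomly selected block sizes of 2/4/6/8"), 1:1. The CRC receives the list and prepares the envelopes.
- **Custody.** "The IC will collect a set of opaque sealed envelopes from CRC as per the serial numbers, a few hours prior to the recruitment". The number in a set is not given.
- **Timing and place.** RAs administer the baseline questionnaire after consent. "The IC will then undertake treatment allocation in a separate room", "using serially numbered, opaque sealed envelopes after they complete their baseline assessment".
- **Opening.** "The IC will open the opaque sealed envelopes (as per the serial numbers) in front of the participants and immediately inform them" of their group.
- **Reporting.** "The IC will inform the CRC the unique identification number of the participant (and no other details) and the intervention allocation group". The CRC keeps the allocation record.

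On the IC's position, the blinding section says that "study team members involved with intervention delivery (IC and yoga instructors) will be aware of" the assigned arm, and that the IC leads the intervention team. Elsewhere in Methods, the IC delivers the Enhanced Usual Care session and makes a home visit when a yoga participant misses two consecutive weekly sessions.

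**The concern.** Custody, opening and reporting all sit with one person, who knows every past allocation and has a practical interest in yoga attendance. The rule on serial order says which envelope comes next. It does not say which woman comes next when several have finished baseline. An IC who follows the text to the letter could still choose who is called in.

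The CRC holds serial number against arm (the list) and ID against arm (the IC's report). No direct link from ID to serial number is stated.

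If women who seemed motivated or able to attend went more often to Yoga-M2, attendance and three-month completion in that arm would look better than under proper randomisation, and the stress comparison could be affected. Preliminary efficacy is one of the primary objectives, and the feasibility results decide whether funding for a larger trial is sought. Adjustment for baseline values, as planned under Statistical methods, would not remove a difference in unmeasured motivation.

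**Working it through.** The plan gives no figure to reproduce here. The check has three parts.

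**1. What is fixed, and when**

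| Item | Stated? |
|---|---|
| Arm behind each serial number | Yes, by the list, before recruitment |
| Order of opening envelopes | Yes, serial order |
| Woman present at opening | Yes |
| Consent and baseline before opening | Yes |
| Order of women when several are ready | No |
| ID tied to a serial number before opening | No |
| Serial number in the report to the CRC | Not listed |
| Delay between opening and report | Not stated |

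**2. How predictable the next arm is**

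Inputs: block sizes 2, 4, 6, 8 and 50 women (protocol); equal probability for each size (assumed). For a block of size *b* with *m* places filled, *o* of them yoga, the chance that the next is yoga is (*b*/2 − *o*)/(*b* − *m*). This is averaged over the block states still possible given the past arms.

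Example: the first envelope is yoga. The chance that the second is usual care is 1 for a block of 2, 2/3 for 4, 3/5 for 6 and 4/7 for 8. The mean is (1 + 0.667 + 0.600 + 0.571)/4 = 2.838/4 = 0.71.

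Over simulated lists of 50, this guesser is right about 68% of the time (50% would be chance). One arm has probability of at least 0.8 in about 22% of allocations, and the next arm is certain in about 2%. A held set contains both arms with probability about 0.61, 0.88, 0.98 and 0.995 for 2, 3, 4 and 5 envelopes.

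**3. What order-steering could do**

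Assume *k* women wait at each session and the IC perceives a trait with SD 1. The woman with the highest value is called when yoga is the better guess, and the woman with the lowest when usual care is. The IC does this every time.

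| Women waiting (assumed) | Mean arm difference in the perceived trait |
|---|---|
| 1 | 0 |
| 2 at every session | 0 |
| 3 | about 0.2 SD (repeat simulations 0.17 to 0.21) |
| 5 | about 0.3 SD (0.27 to 0.31) |

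The zero for one woman is obvious, since there is no choice. For steady pairs it is exact: all block sizes are even, so a pair never straddles two blocks, and within a block either order of the two arms is equally likely. Irregular session sizes lose that protection.

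These are differences in a perceived trait. The shift in an outcome is roughly correlation × trait difference. For assumed correlations of 0.1, 0.3 and 0.5:

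- three waiting: 0.1 × 0.2 = 0.02, 0.3 × 0.2 = 0.06, 0.5 × 0.2 = 0.10 outcome SD
- five waiting: 0.1 × 0.3 = 0.03, 0.3 × 0.3 = 0.09, 0.5 × 0.3 = 0.15 outcome SD

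Both lines are before baseline adjustment.

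**The case against.** The stated safeguards are substantial. Envelopes are opaque, sealed and numbered; the CRC, not the IC, prepares them; and opening happens in serial order in the woman's presence. RAs complete consent and baseline first, so the IC cannot influence who enters. All of this stands.

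Queues may be short. Recruitment is timed to routine antenatal visits, and each woman has an eligibility assessment, an obstetric examination and a questionnaire before allocation. Staggered arrival is plausible, and with one woman at a time there is nothing to steer. The intervention and assessment teams do not discuss participants, so the IC has no stated access to baseline stress scores. This also stands, and it limits the likely size.

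A condensed article may leave envelope signing and the return of used envelopes to the full protocol or an operating procedure. Their absence alone would be no finding. But the article describes the hand-over step by step and lists what is reported, and the point concerns that stated procedure. The words about giving no other details may be meant to protect the woman's confidentiality. They need not forbid reporting the serial number, but the article does not include it.

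Four stronger readings do not hold:

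- **That steering would leave no trace.** The CRC has the list and the IC's reports, and "Study enrollment logs will be maintained by RAs". Enrolment order could be compared with list order. The CRC's weekly consistency checks are not described as doing this, but the records would exist.
- **That the IC knows what the held envelopes contain.** Nothing suggests that the IC receives the list or can read a sealed opaque envelope. Only guessing from past arms is open.
- **That the trait differences can be set beside the protocol's anticipated effect of 0.2.** That effect concerns the contrast between arms in outcome. The two scales match only if trait and outcome correlate perfectly.
- **That recruiters see the sequence because recruitment is counted by arm.** The protocol says that RAs are unaware of allocation, and the by-arm count can come from the CRC's record.

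**Conclusion.** The point holds as a weakness in a stated procedure, worth correcting before recruitment because the correction is cheap. It shows neither that allocation would be subverted nor that the results would be biased.

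An unblinded, intervention-side person could influence which woman gets which arm when three or more are waiting, helped by a guess that is right about 68% of the time. As described, a departure would be hard to detect, though not impossible.

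The trait differences of about 0.2 to 0.3 SD for three to five waiting are worst cases. They assume equally likely block sizes, a constant queue, and an IC who always acts on the guess. The effect on an outcome would be smaller by the unknown correlation, and is zero if women are allocated one at a time.

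**What to change.** Amend Assignment of interventions: allocation (Implementation) as follows.

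1. The CRC keeps the envelopes or the list. After each woman's baseline the IC gives the CRC her ID. The CRC logs that ID and the time against the next serial number, and only then releases the arm.
2. Women are allocated in the trial-ID order set by the RA at consent or baseline.
3. If telephone contact is not possible, the ID, date and time are written on the sealed envelope before opening. The IC reports the serial number with ID and arm, and used envelopes go back to the CRC for reconciliation with the list and the RA enrolment log.

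The cost is about 50 calls, one per woman, or the same number of written entries under the fallback. No new staff are needed: the CRC already holds the list and already receives ID and arm. The drawback is that the CRC must be reachable during recruitment hours.
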